## 7.2 Treatment comparisons

In the semi-factorial early disease randomisation, there will be two pre-specified comparisons:

1. LD-sparing therapy (either DA or MAOBI) versus LD alone, to determine whether LD-sparing therapy is better than LD alone.
2. DA versus MAOBI, to determine which form of LD-sparing therapy is the better.

In the later disease randomisation, there will also be two pre-specified comparisons:

3. DDI (either MAOBI or COMTI) vs DA, to determine whether DDI or DA is better.
4. COMTI versus MAOBI, to determine which form of DDI is the better.

Should one class of LD-sparing therapy or one class of DDI be clearly better than the other, then this drug class will be compared with LD alone in early disease or DA in later disease respectively.

## 7.3. Stratification variables

The early disease randomisation will be 'minimised' within strata defined by whether or not the patient has received previous LD therapy (none, up to one month, one to three months, three to six months), disease stage (Hoehn & Yahr stage - see Randomisation Notepad - for definitions) and by age (<50, 50-59, 60-69, 70-79, 80+ years). Prior hypotheses will be that younger patients and LD-naïve patients derive greater net benefit from LD-sparing therapy. The later disease randomisation will be minimised by age, disease stage (as above) by previous therapy (LD only, DA, MAOBI, COMTI), and by time from initial diagnosis of PD to entry (<4 years, 4-6 years, 6+ years). Subgroup analyses within randomisation strata will be undertaken. Indirect comparisons between types of DA, MAOBI and COMTI will be used to generate hypotheses for prospective testing, rather than to provide definitive answers. Because of the serious dangers of misinterpretation, all subgroup analyses will be interpreted appropriately cautiously.

## 7.4. Data Monitoring Committee: determining when clear answers have emerged

If any of the Parkinson's disease therapies being tested really are substantially better or worse than the others with respect to the main endpoints, or survival, then this may become apparent before the target recruitment has been reached. Alternatively, new evidence might emerge that particular drugs are definitely more, or less, effective than all, or some of, those used in the trial. To protect against this, during the period of intake of the study, interim analyses of major endpoints will be supplied, in strict confidence, to an independent Data Monitoring Committee (DMC) along with updates on results of other related studies, and any other analyses that the DMC may request. The DMC will advise the chair of the Trial Steering Committee if, in their view, any of the randomised comparisons in the trial have provided both (a) "proof beyond reasonable doubt" (see footnote B) that for all, or for some, types of patient one particular treatment is definitely indicated or definitely contraindicated in terms of a net difference in the primary outcome measures, and (b) evidence that might reasonably be expected to influence the patient management of many clinicians who are already aware of the other main trial results. The Steering Committee can then decide whether to close or modify any part of the trial.

Unless this happens, however, the Steering Committee, the collaborators and all of the central administrative staff (except the statisticians who supply the confidential analyses) will remain unaware of the interim results.

If the clinical coordinators are unable to resolve any concern satisfactorily, collaborators, and all others associated with the study, may write through the PD MED Trial Office to the chair of the DMC, drawing attention to any worries they may have about the possibility of particular side-effects, or of particular categories of patient requiring special study, or about any other matters thought relevant.

**Footnote B :** Appropriate criteria of proof beyond reasonable doubt cannot be specified precisely, but a difference of at least three standard deviations in an interim analysis of a major endpoint may be needed to justify halting, or modifying, the study prematurely. If this criterion were to be adopted, it would have the practical advantage that the exact number of interim analyses would be of little importance, so no fixed schedule is proposed.

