# A large randomised assessment of the relative cost-effectiveness of different classes of drugs for Parkinson's disease **PROTOCOL**

[figure not shown]

Parkinson's disease (PD) is one of the commonest causes of disability in older people with at least 8,000 new cases diagnosed each year in the UK alone. Levodopa (LD) controls symptoms for most patients but long-term use is associated with motor complications. A number of other drugs have been used, either alone or with reduced doses of LD, in an attempt to delay the onset of motor complications, or to control complications in later disease once they have developed. These agents have primarily been from three classes of drug: dopamine agonists (DA), monoamine oxidase type B inhibitors (MAOBI) and catechol-O-methyltransferase inhibitors (COMTI).

All of these drugs are beneficial, but there is uncertainty about their relative effectiveness. This is because previous comparative studies included too few patients, most had inadequately short follow-up, and the overall impact of the drugs on the patient's quality of life was not properly assessed. For example, DAs delay the onset of motor complications compared to LD, but this needs to be balanced against poorer control of the symptoms of PD, and worse side-effects - including nausea, hallucinations, sleep disturbance and oedema - which may be more important for patients and carers than motor complications. There are also uncertainties about the role of the potentially neuroprotective MAOBI, selegiline, partly because the UK PDRG trial closed early when an increase in mortality was seen with selegiline compared to LD. However, this has not been confirmed in other studies. Similarly, the COMTI, entacapone, is becoming widely used in later disease, but its efficacy compared to alternative drugs is uncertain. The new DAs and COMTIs are considerably more expensive than either LD or selegiline, and more reliable evidence is needed on the balance of benefits and risks of these drugs to establish their relative cost-effectiveness.

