**MAOB inhibitors:** Inhibitors of dopamine degradation, such as the monoamine oxidase type B inhibitors (MAOBIs), are a second class of drugs that has been widely used as LD-sparing therapy in early PD, or as an add-on to LD in later PD. Trials of selegiline, the most frequently used MAOBI, versus control, with or without LD in both arms, in early PD have consistently shown improvements in the UPDRS and other disability scales with selegiline. These trials have also demonstrated that selegiline treated patients can be maintained on lower doses of LD, and provide some support for a neuroprotective effect of selegiline. However, the largest trial of selegiline plus LD versus LD alone was halted prematurely because of increased mortality in the selegiline arm compared to LD, raising concerns about its use. Subsequent data, including later follow up from the initial adverse study, show no increase in deaths with selegiline and a meta-analysis of all trials confirms this. In total, 283 (24%) deaths have occurred among 1181 selegiline allocated patients and 255 (22%) among 1149 control patients, a non-significant difference (see below).

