## 4. OUTCOME MEASURES

### 4.1. Patient and carer outcomes

The primary outcomes will be the patient's self-evaluation of their functional status and quality of life (using the PDQ-39 questionnaire) and cost-effectiveness (EuroQoL EQ-5D).

Secondary endpoints will evaluate other aspects of functionality, and safety:

- Cognitive function (MMSE)
- Well being of carers (SF-36)
- Resource usage
- Toxicity and side-effects, including mortality rates
- Time to onset of motor complications (early disease randomisation only) and time to surgical intervention or start of apomorphine (later disease randomisation only)
- Capability in older people used in economic evaluation (ICECAP-O)
- Carer Experience Scale (CES)

**PDQ-39:** A clinically and socially meaningful outcome measure needs to address matters of most concern to the individual with PD. The PDQ-39 is a patient-completed questionnaire developed by qualitative in-depth interviews involving patients with PD. It includes items that reflect patients' concerns in relation to eight aspects of PD: mobility, activities of daily living, emotional well-being, stigma, social support, cognition, communication and bodily discomfort. The instrument has been extensively tested for validity, reproducibility and sensitivity to change in both clinic and population survey applications. For example, the instrument has high convergent and discriminant validity in relation to neurologists' assessments of PD severity using conventional clinical scores, such as Hoehn and Yahr, Columbia and UPDRS, and is sensitive to changes considered of importance to patients, but not identified by clinical ratings. It has been translated and used in most European, Australasian and North American countries and has been widely used as an outcome measure in trials of drugs, neurosurgery and nursing care packages.

**EuroQoL EQ-5D:** The main outcome measure for the economic evaluation will be the EuroQoL EQ-5D. Responses will be given valuations derived from published UK population tariffs and the mean number of quality adjusted life-years (QALYs) per patient and incremental QALYs will be calculated. The incremental cost per QALY will then be calculated. All parameters subject to uncertainty will be systematically varied in sensitivity analyses.

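### Section 7.4 names survival as a reason for monitoring, but its criterion for DMC advice covers only the primary outcome measures, which exclude mortality

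*Protocol*

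**What the plan says.** Protocol section 7.4 explains why interim analyses go to the DMC: a therapy may turn out "substantially better or worse than the others with respect to the main endpoints, or survival". Survival is listed there as separate from the main endpoints.

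The same paragraph then sets two conditions, both required, under which the DMC advises the chair of the Steering Committee. Condition (a) is proof beyond reasonable doubt, for all or some types of patient, that "one particular treatment is definitely indicated or definitely contraindicated in terms of a net difference in the primary outcome measures". Condition (b) is "evidence that might reasonably be expected to influence the patient management of many clinicians who are already aware of the other main trial results". Unless this happens, the Steering Committee and collaborators stay unaware of interim results.

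Footnote B says the standard of proof cannot be fixed precisely, and offers three standard deviations on a major endpoint as a guide.

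Section 4.1 defines the primary outcomes as the patient's "functional status and quality of life (using the PDQ-39 questionnaire) and cost-effectiveness (EuroQoL EQ-5D"). The secondary list includes "Toxicity and side-effects, including mortality rates".

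The protocol raises mortality as an issue itself. The opening summary recalls that "the UK PDRG trial closed early when an increase in mortality was seen with selegiline compared to LD", and section 1.2 describes that trial as "halted prematurely because of increased mortality in the selegiline arm compared to LD, raising concerns about its use".

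**The concern.** The purpose sentence and the operative criterion point to different sets of endpoints. A committee that follows the first watches survival as a ground for advice in its own right. A committee that follows the second needs a difference in PDQ-39 or EQ-5D cost-effectiveness, and a difference in deaths alone does not satisfy it. Since the Steering Committee sees nothing until the conditions are met, the criterion also decides who learns of a survival difference.

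This would matter little if the primary outcomes carried the mortality signal. PDQ-39 change does not, because the dead return no questionnaire. QALYs built from EQ-5D do count lost life, so the question is how strongly they do so compared with a direct comparison of deaths.

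**Working it through.** **1. The texts side by side.**

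| Place | Endpoints covered |
|---|---|
| 7.4, purpose sentence | Main endpoints, or survival |
| 7.4, condition (a) | Primary outcome measures |
| 4.1, primary outcomes | PDQ-39; cost-effectiveness (EQ-5D) |
| 4.1, secondary endpoints | Include mortality rates |
| Footnote B | A major endpoint (not defined) |

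Footnote B is attached to the words on proof in (a). It explains how strong the evidence should be and does not change which outcome (a) names.

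**2. The threshold.** Three standard deviations corresponds to a two-sided p of 2 × (1 − Φ(3)) = 0.0027. The protocol states no p-value for this guide, so there is no figure of its own to reproduce.

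**3. The protocol's own mortality figures.** Section 1.2 reports "283 (24%) deaths have occurred among 1181 selegiline allocated patients and 255 (22%) among 1149 control patients, a non-significant difference". The proportions are 283/1181 = 0.2396 and 255/1149 = 0.2219, and the pooled proportion is 538/2330 = 0.2309. The standard error is √[0.2309 × 0.7691 × (1/1181 + 1/1149)] = 0.01746, so z = 0.0177/0.01746 = 1.01. This agrees with the protocol's description.

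**4. How strongly the primary outcomes register deaths.** Suppose deaths differ by just three standard errors.

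Inputs from the protocol:
- 300 per arm (section 7.1).
- 500 per arm, which is the early-disease target of 1500 divided by three.
- 22% as one control mortality, borrowed from the control group in section 1.2.

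Assumptions:
- 10% as an alternative control mortality.
- Mean utility u in survivors of 0.5 to 0.7, with SD s = 0.25, the same in both arms.
- Death scored zero.

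Formulas:
- Deaths: z = (p₁ − p₀)/√[2p̄(1 − p̄)/n].
- Utility: mean m = (1 − p)u, variance v = (1 − p)(s² + u²) − m², and z = (m₀ − m₁)/√[(v₀ + v₁)/n].

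Worked case, n = 300, 10% v 18.6%, u = 0.6:
- Deaths: p̄ = 0.143, SE = √(2 × 0.143 × 0.857/300) = 0.0286, z = 0.086/0.0286 = 3.0.
- Utility: m₀ = 0.5400 and m₁ = 0.4884, a difference of 0.0516. v₀ = 0.9 × 0.4225 − 0.5400² = 0.0887 and v₁ = 0.814 × 0.4225 − 0.4884² = 0.1054. SE = √(0.1941/300) = 0.0254, so z = 2.03.

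| n per arm | Deaths, control v other arm | Excess deaths | z, deaths | z, utility (u = 0.5 / 0.6 / 0.7) |
|---|---|---|---|---|
| 300 | 10% v 18.6% | 26 | 3.0 | 1.82 / 2.03 / 2.20 |
| 300 | 22% v 33.0% | 33 | 3.0 | 2.18 / 2.36 / 2.50 |
| 500 | 10% v 16.5% | 32 | 3.0 | 1.77 / 1.98 / 2.15 |
| 500 | 22% v 30.4% | 42 | 3.0 | 2.15 / 2.34 / 2.47 |

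With 250 per arm the utility z runs from 1.84 to 2.51. If survivors in the two arms are alike, the expected PDQ-39 z is zero in every row.

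These rows start from a death difference that has already reached three standard errors. They say nothing about how likely such a difference is during intake.

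**The case against.** Four points tell against a stronger reading, and each has some force.

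**The rule is not exclusive.** A reader might infer that the DMC is barred from advising on deaths. The text says it will advise if, in its view, the conditions hold; it does not say only if. The DMC may request any analysis, anyone associated with the study may write to its chair about side-effects or other matters, and Footnote B declines to fix a criterion. A sensible committee would probably act on a clear death excess. That stands. But access to data and judgement on whether (a) is met do not change what (a) says, and the confidentiality sentence gives the conditions some gatekeeping effect.

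**Recruitment is not exposed now.** A reader might infer that patients would go on being entered to a harmful class. Interim analyses belong to the intake period. This is Version 10 of August 2019, and the footnote to Table 3 gives a trial end of December 2019 with at least 10 years of follow-up for all. Intake therefore appears to have closed by about December 2009. This limits the urgency.

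**A large excess might not reach the guide during intake.** It is tempting to take 500 per arm, with 3-year mortality of 10% v 17%, as a signal that the rule would suppress. With a full three years of follow-up for everyone, z for deaths is 0.07/√(2 × 0.135 × 0.865/500) = 3.2. Section 7.1 projects 3 to 4 years of intake. With uniform entry over that time and constant hazards −ln(1 − r)/3, where r is the 3-year risk, the probability of death by time A in patients entered uniformly up to A is 1 − (1 − e^(−hA))/(hA). Expected z is then 1.2 to 1.3 at mid-intake and 2.3 to 2.6 at its end, so deaths would not on average meet the guide either. A 10% v 20% excess gives 3.1 to 3.6, but only at the end of intake. Such examples do not show a realised loss.

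**Mortality is raised but not asserted.** The protocol judges the selegiline excess probably due to chance, and its pooled figures give z = 1.01. They do not support reading the protocol as expecting excess deaths. They do show that mortality was a live question when the rule was written.

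**Conclusion.** The inconsistency is real and rests on the text alone: the purpose sentence in 7.4 includes survival, condition (a) omits it, and 4.1 makes mortality secondary. Read literally, a decisive survival difference does not meet (a).

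The primary outcomes only partly fill the gap. PDQ-39 is blind to deaths except through who survives. EQ-5D with death scored zero gives z of about 1.8 to 2.5 when deaths give 3. That range depends on the assumed control mortality of 10% or 22%, survivor utility of 0.5 to 0.7 and SD of 0.25, and other QALY models would give other values.

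The documents do not support the claim that the DMC would have stayed silent, that any patient is currently exposed, or that a signal was missed. This is a defect in the rule as written. It is worth correcting but not critical, and it changes no sample size or planned outcome comparison.

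**What to change.** Reconcile the two sentences of 7.4:

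- Extend condition (a) so that it covers a net difference *in the primary outcome measures, or in survival*.
- In Footnote B, name all-cause mortality by arm among the major endpoints to which the three-standard-deviation guide applies.
- State whether condition (b) must also hold for a survival difference, or whether (a) is then enough.

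The same wording should go into the DMC's terms of reference. Section 6.5 already requires a form within two weeks of a death and supplements this from national mortality statistics, so no data collection or patients are added. The statistical cost is one more monitored endpoint under a guide equivalent to two-sided p of about 0.0027, which is negligible. With intake apparently closed, the main gain is a correct written record of the rule and a sound text for any later trial that reuses it.

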## 8. ORGANISATION

To ensure the smooth running of the trial, and to conform with research governance requirements, it is proposed that each participating centre should designate individuals who would be chiefly responsible for local coordination of clinical and administrative aspects of the trial.

### 8.1. Principal Investigator at each centre

Each Centre should nominate one person to act as the Principal Investigator. Their responsibilities will include:

**Acting as lead clinician for Local Research Ethics Committee (LREC) and Trust approvals for the trial on behalf of their centre:** (See Section 8.4.) Once all necessary approvals have been gained, the Trial Office will send a folder containing all trial materials to the Principal Investigator. Screening and recruitment of patients into the trial can then begin.

**To ensure that all medical and nursing staff involved in the care of Parkinson's disease are well informed about the study:** This involves distributing protocols and patient information sheets to all relevant staff, displaying the wall-chart where it is likely to be read, and distributing the plastic protocol summaries (which can be carried in the pockets of the medical and nursing staff) and the regular newsletters. A regularly updated PowerPoint presentation will be provided for each hospital so that they can be shown from time to time, especially to new staff.

**Chief nursing co-ordinator at each centre:** It is suggested that each participating centre should designate one nurse as local nursing co-ordinator. This person would be responsible for ensuring that all eligible patients are considered for the study, that patients are provided with study information sheets, and have an opportunity to discuss the study if required. The nurse may be responsible for collecting the patient consent form, baseline PDQ-39, EuroQoL EQ-5D, MMSE and SF36 questionnaires. Again, this person would be sent updates and newsletters, and would be invited to training and progress meetings.

### 8.2. Central co-ordination

The PD MED Trial Office at the University of Birmingham Clinical Trials Unit (BCTU) is responsible for providing the trial folders containing all trial materials. These will be supplied to each collaborating centre, after relevant ethics committee approval has been obtained. Additional supplies of any printed material can be obtained on request. The Trial Office also provides the central randomisation service and is responsible for collection and checking of data (including reports of serious adverse events thought to be due to trial treatment) and for analyses.

### 8.3. Cost implications

The trial has been designed to minimise extra costs for participating hospitals. No extra visits to hospital need to be made, and no extra tests are required. The only extra work involved for participants will be informing patients about the study, obtaining their consent to participate, providing baseline data at randomisation, and reporting, infrequently, their progress. Centres can obtain extra support for this work from the NHS Research Support budget and the Trial Office will help them do this. Allowing clinicians to choose whichever DA, MAOBI or COMTI that they would use in their usual daily practice, means that the trial should not involve additional drug costs. Indeed, it could lead to wider use of LD and selegiline, which are considerably less expensive than any of the newer drugs, and thus could lead to substantial future cost savings if LD or selegiline are shown to be of equal or greater efficacy than the newer DAs or COMTIs.

#### **8.4. Research Governance**

The University of Birmingham is the sponsor of the PD MED trial. It has Multi-centre Research Ethics Committee (MREC) approval and Clinical Trials Authorisation from the Medicines and Healthcare Regulatory Authority (MHRA). The Trial Office will assist the Principal Investigator to obtain a site specific assessment from the local research ethics committee (LREC) and approval from the Hospital Trust.

The study will adopt a centralised approach to monitoring data quality and compliance. A computer database will be constructed specifically for the study data and will include range and logic checks to prevent erroneous data entry. The trial statistician will regularly check the balance of allocations by the stratification variables. Source data verification will only be employed if there is reason to believe data quality has been compromised, and then only in a sub-set of practices.

#### **8.5. Indemnity**

There are no special arrangements for compensation for non-negligent harm suffered by patients as a result of participating in the study. PD MED is not an industry-sponsored trial and so ABPI guidelines on indemnity do not apply. The manufacturers of the various PD therapies have not been involved in any way in the design or conduct of the trial. The normal NHS indemnity arrangements for non-negligent liability in clinician-initiated research will therefore operate. It should be noted that NHS Trust and non-Trust hospitals are responsible for any negligent liability because of their duty of care to a patient being treated within their hospital, whether or not that patient is participating in a clinical trial.

